#### Hope for recovery

Generalized mixed effects models will be used to assess the relationship between patients’ group allocation (IG1/IG2/CG/TAU) and hope for recovery at T0, T2, and T3.

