ED psychopathology will be assessed using the Eating Disorders Examination Questionnaire (EDE-Q [32]). The EDE-Q consists of 28 items measuring the cognitions and eating disturbances associated with ED, as well as diagnostically relevant behavioral features of ED. Items can be allocated to four subscales: Restraint, Eating Concern, Shape Concern, and Weight Concern. Mean subscale scores and a mean global score are calculated in order to determine overall eating pathology [32]. The EDE-Q has high internal consistency (α ≤ 0.97) and is sensitive to change [33].Comorbid mental disorders will be assessed using the Patient Health Questionnaire (PHQ-D [34]). The PHQ-D consists of 15 items and is used to screen for symptoms of depressive disorders, panic disorder, and psychosocial functioning. The PHQ-D has excellent criterion validity and good internal consistency for depressive disorders (α = 0.88) [34].Treatment motivation will be assessed using the University of Rhode Island Change Assessment Scale—Short Version (URICA-S [35]). The URICA-S consists of 16 items, measuring four of the six stages of change (i.e., Pre-contemplation, Contemplation, Action, and Maintenance) according to the TTM [8]. Readiness for change scores will be calculated for each patient by summing the mean contemplation, action, and maintenance subscale values of the URICA-S, before subtracting the mean precontemplation subscale value [36]. The URICA-S shows acceptable to good internal consistency (α = 0.61–0.85), as well as strong criterion validity [35].Treatment uptake behaviors will be assessed using a short questionnaire developed for this study. Patients will be asked to select from a list which treatment services they have previously or currently engaged with, and to what extent (e.g., phone contact, appointment made/attended). ED treatment services are varied, including inpatient, partial inpatient, and outpatient treatment in psychiatric/psychosomatic clinics, outpatient psychotherapeutic and nutritionist services, and digital eHealth interventions. For the purposes of this study, treatment uptake will be defined as attending appointments at any of these treatment providers, however, preparatory actions such as researching treatment options and time spent on the wait list will also be assessed.Hope and confidence toward recovery will be assessed using two visual analogue scales. Patients will be asked to indicate how hopeful and confident they are regarding their own recovery. Each patient’s scores will be calculated by measuring the distance (0-100 mm) on the visual analogue scales between the anchor (no hope/confidence) and the patient’s selection, with higher scores indicating greater hopefulness and confidence toward recovery.A post-intervention questionnaire will be used to assess patients’ feedback regarding the authenticity, empathy, and likeability of the person featured in the narrative video, as well as the usefulness of the video(s) as a whole. A subgroup of six patients (determined through Research Randomizer [37]) will also be invited to participate in a semi-structured interview to provide further insights into their perception of the authenticity, empathy, likeability, and usefulness of the video(s), so as to allow for a more thorough and qualitative understanding of how these are experienced by patients.

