### Outcomes

#### Main outcome measures

Main outcome measures of this study will be changes in patients’ treatment motivation and treatment uptake behaviors. Changes in treatment motivation will be measured by comparing patients’ baseline (T0) readiness for change scores (URICA-S) to scores immediately after viewing the videos (T1), at one-week (T2) and three months follow-up (T3). Changes in treatment uptake will be measured by comparing the amount of treatment seeking activities indicated at baseline (T0), at one-week (T2) and three months follow-up (T3).

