#### Secondary ED-related outcome measures

Additional outcome measures will include changes in ED psychopathology, as measured by changes in the scores of the EDE-Q, and changes in patients’ hopefulness and confidence for their own recovery, as measured by increased values in the visual analogue scales immediately after viewing the videos (T1) at one-week (T2) and three months follow-up (T3).

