### Statistical analyses

#### Treatment motivation

Generalized linear mixed effects models will be used to assess the relationship between patients’ group allocation (IG1/IG2/CG/TAU) and their readiness for change scores at T0, T1, T2, and T3.

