#### Treatment uptake behaviors

Pearson’s chi-square tests of contingencies will be used to assess the relationship between patients’ group allocation (IG1/IG2/CG/TAU) and treatment uptake behaviors at T0, T2, and T3.

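### Hope for recovery is defined as an outcome at T1, T2 and T3, but its planned model covers T0, T2 and T3; the two sections must be reconciled

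*Protocol article*

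**What the plan says.** All references are to the protocol article.

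- **Self-report measures.** Hope and confidence are measured on two 0–100 mm visual analogue scales: "Patients will be asked to indicate how hopeful and confident they are regarding their own recovery".
- **Secondary ED-related outcome measures.** Change in hope and confidence is to be read from the "visual analogue scales immediately after viewing the videos (T1) at one-week (T2) and three months follow-up (T3").
- **Statistical analyses, Hope for recovery.** A generalized mixed effects model relates group (IG1, IG2, CG, TAU) to "hope for recovery at T0, T2, and T3". T1 is not listed.
- **Statistical analyses, Treatment motivation.** The corresponding model uses "readiness for change scores at T0, T1, T2, and T3".
- **Statistical analyses, Treatment uptake behaviors.** The chi-square tests use "treatment uptake behaviors at T0, T2, and T3".
- **Procedure.** The treatment-as-usual (TAU) arm is assessed at T0 and T3 only. For T1, the text mentions questionnaires on immediate change in treatment motivation and does not mention hope.

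**The concern.** The article names the visits for the hope outcome twice, and the two lists differ. This is not a detail left to a fuller document: both lists are explicit, and no reason is offered for the difference.

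The intervention is a single video of about six minutes, and T1 is the only assessment directly after it. The Strengths and limitations section says the design allows short-term as well as long-term effects to be examined. Hope is also prominent in the rationale: the Discussion cites an earlier reading study that found no measurable short-term effect on motivation, although most patients reported feelings of hope. The Sample size section gives identifying a meaningful outcome for a larger trial as one of the pilot's main aims. A hope model without T1 has less to offer that choice. While the conflict stands, it is also open whether T1 hope belongs to the planned analysis, and that could be decided after the data are seen.

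**Working it through.** There is no stated figure to reproduce. The check compares the visits in each outcome definition with those in its analysis paragraph.

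| Outcome | Visits in the definition | Visits in the analysis | Agree? |
|---|---|---|---|
| Treatment motivation | T0, T1, T2, T3 | T0, T1, T2, T3 | Yes |
| Treatment uptake | T0, T2, T3 | T0, T2, T3 | Yes |
| Hope for recovery | T1, T2, T3 (as change, so T0 is implied) | T0, T2, T3 | No: T1 missing |

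The uptake definition in the main outcomes section reads "treatment seeking activities indicated at baseline (T0), at one-week (T2) and three months follow-up (T3"), so leaving T1 out of the uptake analysis is consistent. The hope analysis carries the same list as uptake although its definition differs. It may have been carried over from the paragraph above, but the document does not show that.

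**Does the TAU schedule explain the omission?** TAU has neither T1 nor T2. If a missing TAU assessment were the reason for dropping a visit, T2 would have gone as well, yet the hope model keeps it. The motivation model lists all four groups and still includes T1. So the TAU schedule does not explain it.

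**How much is left out, if the scales are given at T1?** The input is 25 patients per group (Sample size section), with every scale completed at every visit.

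- Video-arm patients: 3 arms × 25 = 75.
- Post-baseline hope values in the video arms: 75 × 3 visits (T1, T2, T3) = 225.
- Values at T1: 75 × 1 = 75.
- Share outside the model: 75 / 225 = 1/3, leaving 150 values at T2 and T3.

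With missing assessments the counts fall, so 75 is an upper limit.

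**The case against.** The strongest reply is that the mismatch does not show which section is wrong. Only the secondary outcomes section puts the scales at T1. The Procedure section mentions only motivation there, and the assessment overview (Fig. 2) is not available in the text reviewed. This stands. A reader might infer that T1 hope data are certain to be collected and then ignored; the documents do not establish that, and the figure of 75 values is conditional on it.

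A reader might also infer that the trial is heading for a false finding of no effect on hope because the effect peaks at T1. The article gives no effect size, standard deviation or rate of decay for hope, so any power comparison between T1 and T2 would only return what was assumed. Hypotheses 1 to 4 concern motivation and uptake, hope is secondary, and the immediate effect on motivation is analysed at T1. Nothing prevents T1 hope from being reported descriptively.

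It is likewise tempting to say that the confidence scale enters no analysis. The hope paragraph does name only hope, but the Self-report measures section treats hope and confidence as one item, so the heading may be shorthand. The EDE-Q, another secondary outcome, has no analysis paragraph either, which suggests that the article does not list every secondary analysis. For confidence, this is silence in a condensed text and not a contradiction.

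Finally, the model's treatment of T0 as one of the repeated measurements is not at fault here. Replacing it with baseline-covariate adjustment would be a separate preference that the missing visit does not require.

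None of this removes the conflict between the two lists.

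**Conclusion.** The point holds as an inconsistency between two sections. The definition of the hope outcome includes T1, the planned model does not, and neither the TAU schedule nor anything else in the article accounts for it. If the scales are given at T1, as the outcome section says, the model leaves out the only immediate post-video measurement of this outcome: up to one third (75 of 225) of the post-baseline values in the video arms, assuming 25 per arm and complete data. If they are not given at T1, no data are lost and the error lies in the outcome definition. The text is wrong in one place or the other. The matter should be corrected, but its weight is modest: this is a secondary outcome in a pilot trial, with no hypothesis attached.

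**What to change.** Establish from the assessment schedule whether the two scales are given at T1, then make one of these changes.

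1. **If they are given at T1:** extend the hope model to T0, T1, T2 and T3. State that IG1, IG2 and CG contribute at all four visits and TAU only at T0 and T3, so that contrasts at T1 and T2 are among the video arms. Add that the same model applies to the confidence scale.
2. **If they are not given at T1:** remove T1 from the definition of the hope and confidence outcome, and leave the visits in the hope model as they are. The wording note on the confidence scale is still worth adding.

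Either change costs a sentence or two. The first needs no new data collection if the schedule is as the outcome section states. The choice should be made and recorded before outcome data are examined.

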#### Evaluation of narrative videos

Pearson’s chi-square tests of contingencies will be used to assess the relationship between patients’ group allocation (IG1/IG2/CG) and their evaluation of the narrative videos at T1. Narrative/descriptive syntheses will also be completed, in which patients’ evaluations of the videos will be extracted from interview transcripts and coded under themes.

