**Method:**

This pilot study will examine the effects of patient narrative videos on the treatment motivation and uptake of treatment services for patients with ED. Three narrative videos were developed from the perspectives of (a) a former patient with an ED, (b) an ED specialist, and (c) the same former patient discussing a somatic condition unrelated to ED. Patients will be randomized into three video viewing and one treatment-as-usual group. Effects on treatment motivation will be assessed using the University of Rhode Island Change Assessment Scale (URICA-S) immediately after viewing the videos, as well as one-week and three-month follow-ups. Treatment uptake will be assessed during follow-up using a questionnaire listing possible treatment interactions. A post-intervention questionnaire and semi-structured interviews will be used to assess the feasibility and acceptability of patient narrative videos for this population.

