## Study aims

The proposed study will examine the effects of patient narratives provided in video format for patients with ED. In particular, the role of patient narrative videos on patients’ treatment motivation and uptake of treatment services will be assessed. The study further aims to ascertain the feasibility and acceptability of patient narratives, as well as establishing data to identify suitable outcomes and sample size calculations for a larger trial.

Patients will be randomly assigned to view one of three narrative videos, presented from the perspective of a former and currently recovered patient with an ED (Video A), an ED specialist (Video B), and the same former patient reporting on a somatic condition unrelated to ED (Video C). It is expected that patients who receive access to narrative videos from the perspective of a former patient with an ED (Video A) or an ED specialist (Video B) will show:

stronger increases in treatment motivation (Hypothesis 1).and increased likelihood to engage in treatment uptake behaviors (Hypothesis 2).

compared to patients who receive access to a narrative video unrelated to ED (Video C) or patients who receive access to no videos.

It is further expected that patients who receive access to a narrative video from the perspective of a former patient with an ED (Video A) will show:

stronger increases in treatment motivation (Hypothesis 3).and increased likelihood to engage in treatment uptake behaviors (Hypothesis 4).

compared to patients who receive access to a narrative video from the perspective of an ED specialist (Video B).

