
#### Interventions

The narrative videos used in this intervention were developed collaboratively in a participatory research process with a former patient with an ED, while also being based on the results of a recent systematic review of barriers and facilitators for help-seeking in patients with ED [12]. Preliminary versions of these videos will be trialed in a pre-test study with a healthy student population. The final videos will be approx. six minutes in length (+/- 1 min difference) and feature a person of the same age and gender. The former patient featured in the video is a young woman with a healthy body weight, and it is not explicitly stated which symptoms or ED diagnosis she suffered from. Instead, EDs are discussed as a whole, and the content of the videos focuses on specific aspects of the former patient’s treatment journey, including what motivated her to seek treatment and how her life has changed post-recovery. As part of the pilot study presented here, a parallel 4-arm pilot randomized controlled trial (RCT) approach will be used to evaluate the efficacy of patient narrative videos. Patients will be randomized into one of four groups for the intervention: one group (IG1) will receive access to a video featuring the personal experiences of a former patient with an ED regarding the barriers and facilitators she faced when seeking treatment, with particular focus on stigma, shame, and guilt, as well as the importance of social support. The second group (IG2) will receive access to a video featuring an ED specialist, in which the same barriers and facilitators to treatment presented by the recovered patient will be discussed, but from a professional perspective. The Control Group (CG) will receive access to a video in which the recovered patient will discuss the same barriers and facilitators to treatment, but for a somatic condition unrelated to ED (i.e., torn knee ligament). The remaining patients randomized in the Treatment-as-Usual Group (TAU) will not receive access to any videos.

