#### Evaluation of narrative videos

The suitability of the narrative videos will be determined through a post-intervention questionnaire and qualitative interviews at T1, in which patients will be asked their views on the authenticity, empathy, and likeability of the person featured in the video, as well at the usefulness of the video(s) as a whole.

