### Sample size

Currently, there is limited prior evidence on the effects of patient narratives on the treatment motivation of patients with ED. Existing studies are primarily qualitative in design (e.g., [22]). Further, no studies have previously used video narratives to examine their effect on treatment motivation. The proposed study is a pilot project and as such, its main aims are to investigate the usefulness of the narratives, and to identify a meaningful primary outcome and establish data to allow for sample size calculations for a larger trial. Analogous to similar pilot trials, it is planned to include 25 patients in each study group, resulting in a sample size of 100 patients. Dropout cases will be replaced until the proposed sample size has been recruited.

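### The only stated questionnaire analysis tests whether the three videos are rated differently, which does not address the stated aim of judging whether the eating-disorder videos are acceptable

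*Protocol article*

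**What the plan says.** Three places in the protocol article set the purpose of the video evaluation.

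- Study aims: "The study further aims to ascertain the feasibility and acceptability of patient narratives".
- Sample size, on the pilot: "its main aims are to investigate the usefulness of the narratives", alongside choosing a primary outcome and obtaining data to size a larger trial.
- Outcomes, Evaluation of narrative videos: "The suitability of the narrative videos will be determined through a post-intervention questionnaire and qualitative interviews at T1". The Abstract gives the same two instruments the same job: they "will be used to assess the feasibility and acceptability of patient narrative videos for this population".

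The section of the same name under Statistical analyses then states two analyses. For the questionnaire, Pearson chi-square tests will be used "to assess the relationship between patients’ group allocation (IG1/IG2/CG) and their evaluation of the narrative videos at T1". The second is a narrative or descriptive synthesis in which "patients’ evaluations of the videos will be extracted from interview transcripts and coded under themes". As worded, that synthesis draws on the interviews. Under Self-report measures, the interviews are limited to a few patients: "A subgroup of six patients (determined through Research Randomizer [37]) will also be invited to participate in a semi-structured interview".

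CG is the control video. According to Interventions, the former patient covers the same barriers and facilitators there, "but for a somatic condition unrelated to ED (i.e., torn knee ligament").

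**The concern.** Acceptability, usefulness and suitability are questions about level: do patients find Video A, and Video B, authentic, likeable and useful? The chi-square test asks whether the distribution of ratings is the same in three groups. Its null hypothesis holds when all three videos are rated well and equally when all three are rated badly. The stated analysis therefore answers a different question from the stated aim.

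The choice of groups adds a difficulty for one domain. The control video is about a knee injury, so patients with an eating disorder may well rate it as less useful to them. A significant result for usefulness could then come mainly from the control, whatever patients thought of Videos A and B.

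At stake is what the pilot can report about its own materials before a larger trial. A p-value on either side of 0.05 leaves open whether the eating-disorder videos were well received.

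**Working it through.** **Inputs from the protocol article.** There are 25 patients in each of four groups (Sample size), and 4 × 25 = 100 reproduces the stated total. Three groups see a video, so 3 × 25 = 75 patients rate one. The rated domains are authenticity, empathy, likeability and usefulness. Six patients are interviewed.

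**Assumptions, not in the document.** Each rating is reduced to favourable or not favourable, the significance level is 0.05, and the true favourable rates are as shown below.

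**Step 1: what the statistic depends on.** With n = 25 per group, counts xA, xB, xC and pooled proportion p = (xA + xB + xC)/75, the Pearson statistic on 2 degrees of freedom is

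X² = [(xA − 25p)² + (xB − 25p)² + (xC − 25p)²] / [25p(1 − p)].

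Only departures from the pooled rate enter the numerator.

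- 5/25, 5/25, 5/25: every departure is 0, so X² = 0, p-value 1.
- 23/25, 23/25, 23/25: every departure is 0, so X² = 0, p-value 1.
- 10/25, 10/25, 2/25: p = 22/75 = 0.2933 and 25p = 7.333. The numerator is 2.667² + 2.667² + 5.333² = 42.67 and the denominator is 25 × 0.2933 × 0.7067 = 5.182. X² = 8.23, p-value 0.016. Of those who saw Video A or B, 30/50 = 60% were unfavourable.

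**Step 2: how often it rejects.** Exact enumeration of all outcomes at 25 per group:

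| True favourable rate, A / B / C | Probability of p < 0.05 |
|---|---|
| 90 / 90 / 90% | 0.035 |
| 80 / 80 / 80% | 0.047 |
| 30 / 30 / 30% | 0.050 |
| 20 / 20 / 20% | 0.047 |
| 50 / 50 / 20% | 0.63 |
| 40 / 40 / 10% | 0.73 |
| 50 / 50 / 10% | 0.93 |

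In the first four rows, uniformly good and uniformly poor videos give nearly the same result. In the last three, the test usually rejects although no more than half of viewers favour Video A or B. Those rejections are correct as statements about a difference. They say nothing about level.

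**Step 3: what a per-video estimate gives from the same data.** The Wilson 95% interval is [p̂ + z²/2n ± z√(p̂(1 − p̂)/n + z²/4n²)] / (1 + z²/n), with n = 25 and z = 1.96. For 20/25, z²/n = 0.1537. The centre is (0.80 + 0.0768)/1.1537 = 0.760 and the half-width is 1.96 × √(0.0064 + 0.00154)/1.1537 = 0.151.

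| Favourable | Estimate | Wilson 95% CI |
|---|---|---|
| 5/25 | 20% | 9% to 39% |
| 10/25 | 40% | 23% to 59% |
| 20/25 | 80% | 61% to 91% |
| 23/25 | 92% | 75% to 98% |

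The 5/25 and 23/25 cases, which the test cannot tell apart, have intervals that do not overlap.

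**Step 4: can the interviews supply the level?** If the six are drawn at random from the 75 viewers, the mean is 6 × 25/75 = 2 per video, and the chance that none saw Video A is C(50,6)/C(75,6) = 7.9%. The interviews bear on suitability qualitatively but cannot give a rate.

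**The case against.** The strongest reply is that the document says nothing false. The outcomes section names instruments, not a test, and a chi-square test does assess the relationship it is said to assess. A group-by-rating table also contains the counts for each video, so the favourable proportion for Video A can be read from it, and a full analysis plan may well add descriptive summaries. All of this is fair. It limits the point to a mismatch between the stated aim and the one questionnaire analysis that the article chooses to name. It does not remove it, because what the article fixes for this aim is an association test.

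Including CG is also defensible. Three of the four domains concern the person on screen, and Videos A and C feature the same woman. A versus C therefore varies the topic with the speaker held constant, and A versus B varies the messenger. The expectation of a lower rating for the control applies to usefulness, and there is no similar reason to expect it for likeability or empathy.

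A reader might go further and infer that the plan would declare the eating-disorder videos suitable on a significant p-value, so that the rejection rates of 0.63 to 0.93 above are false-positive rates. The document does not support that. Nowhere does it say that the test decides suitability, and in those scenarios the videos truly differ. Nor does it support the reading that the plan has no means of judging suitability, since the interviews are a second source, or that CG must be taken out of the comparison.

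**Conclusion.** The concern holds as a mismatch between aim and analysis, confined to the questionnaire. The test named in the article is uninformative about the level of acceptance: its rejection probability is about 0.05 whether all videos are at 80% or all at 30%. For usefulness, a significant result may mainly reflect the knee-ligament video. Its p-value should not be offered as evidence that Videos A and B are suitable.

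The figures rest on an assumed favourable/unfavourable split, an assumed 0.05 level and illustrative true rates. The conclusion does not, because a test of equality across groups carries no information on level for any response format. An ordinal test across the same three groups would have the same limitation. No hypothesis on motivation or treatment uptake is affected. The point matters because acceptability and usefulness are among the reasons given for running the pilot.

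**What to change.** In the statistical section on evaluation of the videos, make the primary questionnaire analysis a per-video estimate. For each item, report the favourable proportion or the mean with a 95% confidence interval for Video A and for Video B, with Video C shown alongside.

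Keep the between-video comparison as supportive. State that it addresses differences between videos (A versus B for the messenger, A versus C for the topic with the same speaker) and not suitability.

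A pre-set acceptability level is optional. If one is wanted, 25 per video supports only a coarse rule, and its performance depends on the level chosen. Requiring at least 18/25 against an illustrative 50% has one-sided error 0.022 and power 0.89 at a true 80%. Requiring at least 20/25 against 60% has error 0.029 and power 0.62 at a true 80%.

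The cost is a reworded paragraph and slightly more reporting, with no new patients, visits or data. The intervals will be wide (61% to 91% around an observed 80%), and the report should say so.
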